## Abstract

**Background:**

The approach to induction of labour differs internationally, with timing of amniotomy being controversial. Some institutions favour performing artificial rupture of membranes prior to commencement of oxytocin infusion, with the belief that the labour will progress more efficiently. In other institutions, the approach recommended is for oxytocin infusion with intact amniotic membranes until the person has reached the active phase of labour, citing risk of infection with early amniotomy. Current evidence is inconclusive. We are performing a randomised controlled trial assessing whether delaying amniotomy until the active phase of labour can decrease the rate of chorioamnionitis.

**Methods:**

This is a randomised controlled trial at a single centre in New Zealand. Pregnant people undergoing induction of labour at ≥ 37 weeks gestational age with intact membranes and a singleton gestation are eligible for the trial. Participants are randomised to ‘Early’ amniotomy, at the commencement of oxytocin infusion, or to ‘Late’ amniotomy, when they have reached a cervical dilation of 6 or more centimetres or when they have been receiving oxytocin infusion for 12 h. The primary outcome of the trial is chorioamnionitis. To detect a decrease in chorioamnionitis from 9 to 3% with a power of 80% and a 95% CI, we will require 488 participants in total, randomised in a 1:1 ratio.

**Discussion:**

If delaying amniotomy reduces the rate of chorioamnionitis, this is important to inform future practice. Chorioamnionitis entails risk to both the pregnant person and the fetus and is an important contributor to neonatal sepsis, neonatal intensive care unit admission, maternal sepsis, caesarean, wound infection and postoperative infective complications. Conversely, if the rate of chorioamnionitis is not affected by timing of amniotomy, this will allow for safe individualization of care.

**Trial registration:**

The trial is registered on the Australian and New Zealand Clinical Trials Registry, anzctr.org.au. Full registry title is ‘Impact of early versus late artificial rupture of membranes during oxytocin induction of labour on the incidence of chorioamnionitis: A randomised controlled trial’. Trial ID: ACTRN12621000405819. Date registered 14 April 2021.

## Introduction

### Background and rationale {6a}

Induction of labour (IOL) is one of the most common procedures performed in pregnant people, with approximately 40% of labours being induced at Te Toka Tumai Auckland [1]. There are multiple induction agents that may be used for IOL, including prostaglandins, catheters and oxytocin infusion [2–5]. There appears to be regional variation in induction and labour management in relation to artificial rupture of membranes (ARM), with some centres performing ARM liberally, while other centres are quite restrictive in the practice. People undergoing induction of labour in New Zealand commonly have an ARM early during the process, often immediately prior to oxytocin infusion. This differs from other settings where ARM is performed after the patient enters active labour, or not at all (meaning that spontaneous rupture of membranes [SRM] is awaited). Two Cochrane reviews have investigated the role of ARM. One review assessed performance of ARM during spontaneous labour and one assessed ARM to induce labour [6, 7]. Neither identified a clear benefit to ARM and hence it was not recommended by either group of authors [6, 7].

One potential issue with performing an early ARM is that the protective barrier between the uterine cavity and the vagina (the amniotic membrane) is now interrupted, allowing for ascent of bacteria from the vagina into the uterus. Moreover, this practice permits the fluid ‘cushion’ surrounding the fetus to be released and theoretically provides a greater chance for umbilical cord compression, leading to fetal heart rate decelerations. These theories that lead to a concern about early amniotomy are supported by evidence from three small trials [8–10].

The first trial, involving 209 participants in the United States, identified a marked difference in people undergoing amniotomy in rates of chorioamnionitis (22.6% versus 6.8%, *p* = 0.002 in the early ARM versus late ARM groups, respectively) and variable decelerations (19.6% versus 6.4%, *p* = 0.08 in the early ARM versus later ARM groups, respectively) [8]. The second trial including 168 people recruited in Israel identified an elevated risk of intrapartum fever (which we consider to be a surrogate for chorioamnionitis) in the early ARM group (8.7% versus 2.3%, RR 1.69; 95% CI 1.15–2.5) in addition to a higher risk of caesarean birth in the early ARM group (25% versus 7.9%, RR 1.74; 95% CI 1.30–2.34) [9]. Lastly, a trial from India in which 150 women were randomised indicated shorter labours (7.35 h versus 11.66 h, *p* = 0.000) but a significant increase in caesarean rate (2.7% versus 10.7%, *p* = 0.049) when ARM was performed early [10].

A further two trials indicated that early and late amniotomy yielded equivalent outcomes between groups for rates of infection [11, 12]. The first of these trials was carried out in Canada and was unfortunately closed to recruitment at 143 participants after 3 years because of the low recruitment rate [11]. The primary outcome was rate of caesarean birth, which did not differ for nulliparous (18 vs 17%, *p* = 0.91) or parous (0 vs 3%, *p* = 1.0) people in the early and late amniotomy groups, respectively. This trial also indicated a non-significant trend towards fewer fevers in the early amniotomy group (3 vs 25%, *p* = 0.05). The second of these trials was performed in the United States and included 585 participants, all of them nulliparous [12]. The primary outcomes of the trial were time from induction to birth (19.0 vs 21.3 h, *p* = 0.04) and percentage of people who gave birth within 24 h (68 vs 56, *p* = 0.002) in the early and the late amniotomy groups, respectively. Chorioamnionitis rates were equivalent between groups (11.5 vs 8.5%, *p* = 0.22). However, in this trial, most people in the early ARM group had ARM at 3 cm cervical dilation, making the trial incomparable to the New Zealand context, where amniotomy is frequently performed as soon as feasible, which is at a cervical dilation that permits the insertion of an amniohook instrument (often 1–2 cm of dilation).

The findings of these trials are of significant import in the approach to IOL in New Zealand and internationally. Chorioamnionitis is a common occurrence in induced labour [8, 9]and is often a factor in the decision to perform an emergency caesarean birth and then in subsequent surgical infective complications. Chorioamnionitis entails maternal risks and requires treatment for both the mother and the infant during and after birth. Caesareans change the risks for the mother and infant but generally both have a higher risk of complications when a caesarean is performed after the commencement of labour (as occurs in the setting of labour induction). Chorioamnionitis is a risk factor for cerebral palsy and neonatal encephalopathy, even in term foetuses [13, 14].

Trial data regarding timing of amniotomy and infective and operative risk is mixed, showing either a benefit to delaying the procedure or no significant difference in outcomes between groups. There is some indication that induced labour may be slightly shorter with earlier amniotomy. None of the trials has been carried out in New Zealand, and both trials indicating equivalent outcomes in the early and late amniotomy groups were methodologically quite dissimilar to usual labour management in obstetric units in New Zealand. Indeed, the New Zealand national guideline on induction of labour identified timing of amniotomy as a research gap [15]. Irrespective, the procedure is performed on approximately 15,000 people who have IOL in New Zealand each year [15]. Therefore, ascertaining the ideal timing of ARM is important. To answer the question of whether early amniotomy causes an increased rate of chorioamnionitis in the setting of IOL, we are performing a randomised controlled trial. If our study indicates benefit to delaying amniotomy until active labour, this is a low-cost intervention (changing the timing of something that is done anyway) which could provide great benefit for women and babies.

### Objectives {7}

The objective is to assess the rate of chorioamnionitis in women undergoing early versus late ARM.

### Trial design {8}

The ARM trial is a randomised controlled trial being performed at a single institution in New Zealand, Te Toka Tumai Auckland. Participants undergoing oxytocin IOL are randomised to either ‘Early ARM’ or ‘Late ARM’ in a one-to-one ratio, stratified by parity (parity = 0 or ≥ 1). The primary hypothesis is that people undergoing ‘Late ARM’ will have a lower chance of developing chorioamnionitis than those people undergoing ‘Early ARM’.

## Methods: participants, interventions and outcomes

### Study setting {9}

This is a single-centre RCT, being carried out at Te Toka Tumai Auckland. The hospital is located in the central Auckland urban catchment and provides both assessment and birthing units as well as a level 3 NICU. Te Toka Tumai Auckland provides care to approximately 6000 people giving birth each year.

### Eligibility criteria {10}

Inclusion criteria:Pregnant people with a live singleton cephalic presentationPlanning IOL at ≥ 37 weeks gestationIntact membranesCardiotocography normalRequire oxytocin for induction of labour

Exclusion criteria:Previous caesarean birthMajor fetal congenital anomaly or known chromosomal abnormalityFetal growth restriction with absent or reversed end-diastolic flos noted on umbilical artery Doppler (fetal growth restriction with abnormal pulsatility index of the middle cerebral artery or umbilical artery or abnormal cerebroplacental ratio is permissable).

**Prior criterion was any participant in the OBLIGE study. This study is now completed [16]

### Who will take informed consent? {26a)

Patients identified as eligible are approached for inclusion for the trial when they present to the Women’s Assessment Unit at the Auckland City Hospital. Lead maternity carers (LMCs) who are either midwives or obstetricians, within the community, are aware of the trial and have frequently discussed it with the potential participant prior to their arrival to the unit. Once admitted for IOL, people are approached regarding the trial by either a research team representative or by an obstetric or midwifery team member. The trial procedures and purpose are reviewed with the patient, and a copy of the trial participant information sheet and consent form (PIS/CF) and pamphlet are provided for review. After an opportunity to discuss and ask questions, patients may choose to participate. Written informed consent is required for participation in the trial.

### Additional consent provisions for collection and use of participant data and biological specimens {26b}

N/A. Data will not be utilised in ancillary studies, and biological specimens are not collected.

## Interventions

### Explanation for the choice of comparators {6b}

The intervention groups in this trial are ‘Early’ and ‘Late’ timing of amniotomy. Standard care in our hospital is early amniotomy. The primary hypothesis is that people undergoing ‘Late ARM’ will have a lower chance of developing chorioamnionitis than those people undergoing ‘Early ARM’.

### Intervention description {11a}

Amniotomy is a common obstetric procedure during which a gloved hand is used to perform a vaginal examination. Once the cervix is located and the examiner’s fingers are placed inside the dilated portion, against the amniotic membrane, a plastic amnihook is advanced along the fingers. The instrument has a sharp ‘hook’ at the end. This end of the implement is utilised to cause a small tear in the amniotic membrane, after which time some of the amniotic fluid is usually felt to be expelled vaginally.‘Early ARM’ group: ARM is performed either prior to or within 60 min of commencement of oxytocin infusion‘Late ARM’ group: oxytocin infusion is commenced first, and ARM is performed at ≥ 6 cm cervical dilation or if the participant has been receiving oxytocin infusion for at least 12 h and has not yet reached 6 cm of cervical dilation

### Criteria for discontinuing or modifying allocated interventions {11b}

Participants may have modification to timing of amniotomy as the clinician caring for them sees fit. For example, a person allocated to having a ‘Late’ ARM may have this performed earlier than anticipated if a fetal scalp electrode needs to be placed for a clinical indication.

Participants can withdraw from study procedures at any time. This may include withdrawal for clinical procedures (for example requesting an ‘Early ARM’ though they are randomised to ‘Late ARM’) but with consent for continued use of data. Participants may also withdraw the use of their data from the trial. As a contingency for participant withdrawal from both clinical procedures and use of data, recruitment of 500 participants is planned (power calculation for the trial requires 488 participants).

### Strategies to improve adherence to interventions {11c}

Staff on the unit have had in-person education on the study groups. Additionally, written materials are available at all times on the delivery unit specifying the treatment per study arm.

### Relevant concomitant care permitted or prohibited during the trial {11d}

Clinical care during the trial is per hospital clinical guidelines.

### Provisions for post-trial care {30}

None outlined to participants. New Zealand has a public health care system. Treatment injuries (including injuries sustained during birth) are assessed and covered by the Accident Compensation Corporation (ACC) in New Zealand.

### Outcomes {12}

Primary outcome:

**Table Tabb:** 

Outcome measure	Timepoint	Method of ascertainment
Diagnosis of chorioamnionitis *Chorioamnionitis is defined as maternal temperature of greater than or equal to 38 °C OR 2 maternal temperatures of > 37.5 °C AND the choice to treat for chorioamnionitis with antibiotics	By birth of neonate	This outcome will be assessed via medical record review. Diagnosis and treatment of chorioamnionitis is recorded in the medical chart as well as the medication chart

Secondary outcomes:

**Table Tabc:** 

	**Outcome measure**	**Timepoint**	**Method of ascertainment**
1	Caesarean birth—overall incidence of caesarean birth post-induction	By birth of neonate	This outcome will be assessed via medical record review. An operative report will be recorded in the event that a caesarean is performed
2	Caesarean birth for fetal heart rate abnormality	By birth of neonate	This outcome will be assessed via medical record review. An operative report will be recorded in the event that a caesarean is performed
3	Caesarean birth for labour dystocia	By birth of neonate	This outcome will be assessed via medical record review. An operative report will be recorded in the event that a caesarean is performed
4	Fetal heart rate abnormalities	By birth of neonate	This outcome will be assessed via medical record review. An operative report with the operative indication(s) will be recorded in the event that a caesarean or instrumental vaginal birth is performed for fetal heart rate abnormalities. The midwife also performs a checklist after each birth which details the presence or absence of fetal heart rate abnormalities
5	Fetal heart rate abnormalities resulting in fetal scalp lactate sampling	By birth of neonate	This outcome will be assessed via medical record review. Fetal scalp lactate sampling and the results of the sampling are entered into the medical record
6	Fetal heart rate abnormalities resulting in instrumental vaginal delivery	By birth of neonate	This outcome will be assessed via medical record review. An operative report with the operative indication(s) will be recorded in the event that a caesarean or instrumental vaginal birth is performed for fetal heart rate abnormalities. The midwife also performs a checklist after each birth which details the presence or absence of fetal heart rate abnormalities
7	Maternal temperature greater than or equal to 38 °C	By birth of neonate	This outcome will be assessed via medical record review. The observation chart contains recordings of the maternal temperature readings
8	Maternal temperature of > 37.5 °C on single occasion during labour	By birth of neonate	This outcome will be assessed via medical record review. The observation chart contains recordings of the maternal temperature readings
9	Maternal temperature of > 37.5 °C on two occasions during labour	By birth of neonate	This outcome will be assessed via medical record review. The observation chart contains recordings of the maternal temperature readings
10	Postpartum endometritis	By diagnosis made within 7 days of birth	This outcome will be assessed via medical record review. The data will be available in the clinical record and treatment will be available in the medication chart
11	Infant born with 5-min Apgar scores < 7	By data imputed 5 min post-delivery	This outcome will be assessed via medical record review. The neonatal APGAR scores are recorded in the delivery summary
12	Infant born with abnormal cord blood lactate levels greater than or equal to 4.0	By data imputed from birth	This outcome will be assessed via medical record review. The neonatal cord blood gas readings are recorded in the delivery summary
13	Infants born with abnormal cord blood pH ≤ 7.10	By data imputed after delivery	This outcome will be assessed via medical record review. The neonatal cord blood gas readings are recorded in the delivery summary
14	Time to vaginal delivery	By birth of neonate	This outcome will be assessed via medical record review. The duration from start of oxytocin to delivery of the neonate will be calculated and presented as a median
15	Time from rupture of membranes to vaginal birth	By birth of the neonate	This outcome will be assessed via medical record review. The duration from start of rupture of membranes to the delivery of the neonate will be calculated and presented as a median
16	Neonatal intensive care unit (NICU) admission	By discharge from hospital of neonate	This outcome will be assessed via medical record review. NICU admission results in both a history and physical record and a discharge summary
17	Cost-effectiveness	By discharge of both mother and baby from hospital	This outcome will be assessed via medical record review. The cost of length of stay (in days) for both mother and baby will be assessed

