### Participant timeline {13}

Person is identified as eligible.

↓

Discussion regarding study with clinician or member of the research team.

(after discussion with clinician).

Participant information sheet and consent form provided.

↓

Examination that assesses ARM feasible.

(either at presentation or after cervical preparation for induction of labour).

*People who go into labour from cervical preparation who no longer require oxytocin or with people who undergo SRM prior to randomisation are screen fails and are not randomised.

↓

Randomisation (online randomisation system [17]).

↓

IOL commences.

(*Early ARM group*: oxytocin infusion started and ARM within 60 min).

(*Late ARM group*: oxytocin started and ARM at 6 cm or more cervical dilation or at 12 h of oxytocin infusion).

↓

Participant completes post-induction survey regarding their birth experience.

↓

Data collection baseline demographics, labour and birth, maternal outcomes and neonatal outcomes to discharge from hospital.

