### Implementation {16c}

The randomisation is computer generated and outsourced to the Liggins Institute Clinical Data Research Hub. The research midwives and investigators who enrol participants do not have access to the randomisation schedule. People can consent to the study at admission to the hospital for induction of labour. At Te Toka Tumai Auckland, IOL patients are initially seen in the Women’s Assessment Unit and cervical preparation undertaken in that location. When they are found to have a favourable cervical examination, they await transfer to delivery unit.

Once a participant arrives on delivery unit and is ready to commence induction with oxytocin, the midwife caring for the participant on delivery unit accesses the computerised randomisation site. The study intervention is then assigned electronically.

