## Statistical methods

### Statistical methods for primary and secondary outcomes {20a}

Descriptive data will be presented on the study groups.

Analyses will follow the principle of intention-to-treat. Missing data will not be imputed and will be presented as missing for these variables.

Additionally, a per-protocol analysis will also be undertaken, which will exclude from analysis any participant in the ‘Early’ ARM group who had ARM performed greater than 60 min after commencement of oxytocin infusion and any participant from the ‘Late’ ARM group who had ARM performed before 6 cm dilation or 12 h from oxytocin commencement due to trial procedure withdrawal. Participants who have protocol deviations for clinical indications (for example to place a fetal scalp electrode due to fetal heart rate abnormalities) will remain in the analysis.

Primary and secondary outcome analyses will be adjusted for the stratification variable using regression techniques, and outcomes presented as relative risks or mean differences with 95% confidence intervals.

A *p* value of 0.05 will be considered statistically significant. There are multiple secondary outcomes. These will be reported with *p* values without adjustment for multiplicity but recognised as exploratory.

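### The time-to-delivery outcomes start the clock at a point that depends on the arm, are labelled as vaginal births only, and carry two incompatible summary measures

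*Protocol article*

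**What the plan says.** The secondary outcomes table labels outcome 14 "Time to vaginal delivery" and defines it thus: "The duration from start of oxytocin to delivery of the neonate will be calculated and presented as a median". Outcome 15 is labelled as the time from membrane rupture to vaginal birth, and its ascertainment cell reads: "The duration from start of rupture of membranes to the delivery of the neonate will be calculated and presented as a median". In both rows the label restricts to vaginal birth, while the ascertainment cell speaks of delivery without naming a mode.

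Intervention description {11a} says that in the Early group "ARM is performed either prior to or within 60 min of commencement of oxytocin infusion". In the Late group oxytocin always comes first. Participant timeline {13} describes the Early group only as "oxytocin infusion started and ARM within 60 min", without the option of amniotomy first. Under Implementation {16c}, participants are randomised at a point common to both arms: "Once a participant arrives on delivery unit and is ready to commence induction with oxytocin".

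Statistical methods {20a} has primary and secondary analyses adjusted for parity by regression, with "outcomes presented as relative risks or mean differences with 95% confidence intervals". Secondary outcomes get p-values without multiplicity adjustment and are declared exploratory. Caesarean birth is itself secondary outcome 1.

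**The concern.** A randomised comparison of labour duration needs a start point that allocation cannot move and a set of participants that allocation cannot select. Outcome 14 lacks the first, and by their labels outcomes 14 and 15 both lack the second. Time spent between amniotomy and oxytocin counts for nobody in the Early arm, and the Late arm has no such interval under the protocol. Dropping caesareans removes participants on the basis of an event that the trial itself expects may differ by arm. The effect measure is then stated in two ways that do not match.

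Labour duration matters here beyond its exploratory status. The Background names a slightly shorter labour as the possible advantage of early amniotomy. The Discussion says that staff beliefs about timing and labour length have hampered recruitment. A reader weighing any infection benefit of waiting will look at this outcome first.

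**Working it through.** The plan gives no figure for the time outcomes. Its only related figure, 244 per arm (488 in total), is for the primary outcome. It reproduces closely: 245 per arm by the pooled two-proportion formula for 9% versus 3%, and 79.9% power at 244. It has no bearing on this point.

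Each feature is checked below with no true difference in labour length between arms. Differences are Early minus Late.

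**1. The clock (outcome 14).** If a share *s* of the Early arm has amniotomy *g* hours before oxytocin, and total time from randomisation is the same in both arms, the oxytocin clock shifts the Early mean by −*s* × *g*. The documents give neither *s* nor *g*. Assumed range: *s* from 25% to 100%, *g* from 0.5 to 2 h.
- Smallest: 0.25 × 0.5 = 0.125 h. The simulated median shift is −0.12 h.
- Middle: 0.5 × 1 = 0.5 h. The simulated median shift is −0.49 h.
- Largest: 1 × 2 = 2 h. The simulated median shift is −2.0 h.

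The simulation assumed lognormal times with median 14 h and log-SD 0.5. Timing from randomisation gives 0 in every case.

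**2. Vaginal births only (outcomes 14 and 15), illustrated on outcome 14.** The caesarean rates are from the trials summarised in the Background: 25% versus 7.9% (the trial of 168 people) and 18% versus 17% (nulliparous participants in the Canadian trial). Assumed: lognormal times, median 19 h, log-SD 0.5, identical in both arms.

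Upper bound, with every caesarean among the slowest labours. The vaginal-only median is 19 × exp(0.5 × z(0.5 × (1 − c))), where c is the caesarean rate and z(p) the standard normal quantile.
- c = 25%: z(0.375) = −0.319, giving 16.2 h.
- c = 7.9%: z(0.4605) = −0.099, giving 18.1 h. The difference is −1.9 h.
- c = 18% versus 17%: 16.96 versus 17.07 h. The difference is −0.1 h.

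Partial link between caesarean and slow labour (logistic slopes of 0.5, 1 and 2 per SD of log time):
- 25% versus 7.9%: −0.7, −1.2 and −1.7 h.
- 18% versus 17%: −0.04, −0.07 and −0.10 h.

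A second model (median 14 h, log-SD 0.5, latent correlation 0 to 0.6) gives:
- 25% versus 7.9%: about 0 to −1.0 h.
- 18% versus 17%: about 0 to −0.06 h.
- Equal rates of 20%: 0.
- 7.9% versus 25%, that is, more caesareans in Late: about 0 to +1.0 h.

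For scale, the largest cited trial reported 19.0 versus 21.3 h from induction to birth, a difference of 2.3 h.

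**3. The summary measure.** A regression mean difference estimates a contrast of means. On the assumed 14 h lognormal the median is 14.0 h and the mean 15.9 h, so the two describe different quantities. The mismatch does not itself favour an arm.

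**4. Outcome 15.** Suppose Early rupture falls 0 to 1 h after oxytocin starts, and Late rupture comes at the earlier of 6 cm or 12 h, with 6 cm assumed to be reached 60% to 80% of the way through labour. Identical labours then give medians of 13.5 h in Early against 2.8 to 5.6 h in Late. Allocation largely sets this outcome.

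**The case against.** A reader might infer that these features together make the comparison favour Early amniotomy by construction. The documents do not support that. Only the outcome 14 clock has a fixed direction. The vaginal-birth restriction follows the caesarean rates, and the cited evidence is mixed: the Canadian trial shows almost no difference, and the printed figures of the Indian trial (2.7% versus 10.7%) do not match the order of its wording. The median/mean conflict has no direction, and outcome 15 runs longer in Early.

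The sizes can also be challenged, and fairly. The 1.9 h figure is a worst case. Caesareans for fetal heart rate abnormality (secondary outcome 2) need not be slow labours, and the 19 h median comes from an all-nulliparous trial timed from induction. The clock effect may be small: the Background describes amniotomy as often immediately preceding oxytocin, the abstract places it at oxytocin commencement, and randomisation waits until the participant is ready for oxytocin. Early participants who labour after amniotomy alone would have no start time, but the documents do not say that this happens.

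The details of competing-risk modelling belong in a statistical analysis plan, and a descriptive median can sit beside a regression estimate. Hospital days, used for cost-effectiveness, avoid both the oxytocin clock and the vaginal-birth restriction.

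These arguments limit direction, size and severity. They do not remove an arm-dependent start point, labels that disagree with their own definitions, or a fixed effect measure that does not match the fixed summary.

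**Conclusion.** The point holds as a defect in how two exploratory secondary outcomes are defined.
- **Clock:** outcome 14 drops any amniotomy-to-oxytocin interval from Early only. The shift is −0.12 to −2.0 h over the assumed range; the true size cannot be found from the documents. The intervention description and the participant timeline differ on whether amniotomy may come first, and must be reconciled.
- **Selection:** read by their labels, outcomes 14 and 15 condition on vaginal birth. For outcome 14 this gives about 0 to 1.9 h in favour of Early at 25% versus 7.9%, at most about 0.1 h at 18% versus 17%, and the reverse if Late has more caesareans. All of this rests on assumed lognormal times and an assumed link between caesarean and slow labour.
- **Summary measure:** a median in the outcome table and a mean difference in the methods need aligning.
- **Outcome 15:** it mainly measures how far apart the arms were kept. That is useful given the protocol violations reported in the Discussion, but it is not evidence on labour length.

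The primary outcome and the sample size are not affected.

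**What to change.** Before data lock:
1. Time outcome 14 from randomisation in both arms. This assumes that the electronic randomisation system records the time, which the article does not state and which should be confirmed.
2. Include all randomised participants. Treat caesarean as a competing event for vaginal birth, using cumulative incidence or the proportion delivered vaginally by fixed times, adjusted for parity. Report time to any birth alongside.
3. Make labels and ascertainment cells agree on mode of birth, and align the outcome table with section {20a} on one effect measure suited to skewed times.
4. Report outcome 15 descriptively, as a measure of separation between arms.
5. Reconcile sections {11a} and {13} on the order of amniotomy and oxytocin in the Early arm.

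If randomisation times are held, the cost is wording and slightly more analysis, with no new outcome data. The result is less directly comparable with published oxytocin-to-delivery times; that interval can be kept as a descriptive figure.
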